### Data collection and follow-up

For all patients, follow-up assessment will be performed until recurrence and/or death. For the study, the recurrence free survival will be assessed at 3 years. For patients included in the present trial, the follow-up will be systematic and performed thereafter this period according to the good clinical practices. The follow-up schedule and investigations proposed for the present study are those recommended by the FFCD [8].

Every 6 months, the following investigations will be performed: tumor assessment, CEA measurement, survival status, additional cancer therapy. Moreover, the following assessments will be performed during the follow-up: colonoscopy 3 years after surgery then every 3 to 6 years, assessment of neurological toxicity, and assessment of electrolytes (magnesium, calcium, potassium) at the second follow up visit (12 months after surgery) if still abnormally decreased at end of treatment assessment.

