**Fig. 2 Fig2:**
[figure not shown]
The Tumor Regression Grade (TRG), as simplified to three categories by Ryan (19). TRG1: Major response; TRG2: Intermediate response; TRG3: No response

Secondary endpoints are the following: (i) postoperative morbidity (occurring within 60 postoperative days) graded 0 to 5 according to the Clavien-Dindo classification [20]. If grade 3 or 4 complications occur at a rate ≥ 10 % in either neoadjuvant chemotherapy arm, the arm will be declared hazardous (see section statistical analysis); (ii) the safety of neoadjuvant therapy will be assessed by the systematic collection of toxicity data related to chemotherapy, the total number of cycles administered pre-operatively (documenting reasons for early termination), and the systematic collection of GI symptoms. In addition, complications related to the in situ tumor that could delay the date of surgery or require emergency colonic surgery or stenting, will be documented. These parameters will be evaluated after administration of the first cycle of neoadjuvant chemotherapy; (iii) Regression-free survival at 3-years defined as the time interval between the date of randomization and the date of first recurrence (local, regional or metastatic) or date of death (all causes) if no recurrence; (iv) Disease-free survival at 3 years defined as the time interval between the date of randomization and the date of first recurrence (local, regional or metastatic), or second cancer, or the date of death without recurrence (all causes) and date of second cancer; (iv) Quality of life (evaluated using the EORTC quality of life (QoL) QLQ-C30 and QLQ-CR29); Quality of life will be assessed at the inclusion, after neoadjuvant chemotherapy, at 1 month after surgery and every 6 months thereafter. The QLQ-C30 consists of 30 items with both multi-items scales and single item measures. The internal validation of QLQ-C30 allowed to identify 15 scales and to generate 15 scores: 5 scores of functional scale (physical functioning, role functioning, cognitive functioning, emotional functioning, social functioning), a global health status scare, a financial difficulties scale and 8 symptoms scale (fatigue, nausea/ vomiting, pain, dyspnoea, insomnia, appetite loss, constipation, diarrhoea). These scores vary from 0 (worse) to 100 (better) for functional and global health scale and from 0 (better) to 100 (worse) for symptoms scales. Targeted QoL dimensions for this trial are Global Health, physical and emotional functioning, fatigue and pain of QLQ-30 as well as dimensions of CR29. A 5 points difference in QoL is considered as minimal clinically important difference (MCID). Time to QoL deterioration will be defined as time interval between randomization and first decrease in QoL score greater or equal to 5 points. Patients without QoL decrease greater or equal to 5 points will be censored at the last follow-up. (v) Quality and completeness of the surgical excision evaluated on pathological criteria (number of lymph nodes examined, the completeness of removed mesocolon, surgical margins); (vi) radiological staging and radiological response. The initial radiological staging based on abdominopelvic CT scan will be compared with the histopathological pTNM staging in the control group. CT scan images will be interpreted by the individual study centers, and reviewed by 2 of the 3 members of our Central Review Committee of Radiology. This dual independent reading will assess inter-observer reproducibility of the radiological response to treatment with a test of concordance. The radiological response will be defined by RECIST (v1.1) [21] on CT scan and evaluated in the neoadjuvant chemotherapy arms. These criteria will be applied to the primary colon tumors (largest diameter) and lymph nodes (smallest diameter). The sum of the diameters of the target lesions will be determined on the pretreatment CT scan (initial staging) and compared with the sum of these measures on the reevaluation CT scan (performed within 3 weeks after the completion of neoadjuvant chemotherapy). Interpretation of the reevaluation CT scan will be centralized and carried out independently by 2 of the 3 members of our Central Review Committee of Radiologists blinded to the pretreatment CT scan staging. This dual independent reading will assess inter-observer reproducibility of RECIST criteria applied to CC, and determine if there is a difference in radiological response between the two chemotherapy regimens under investigation in the study; (vii) Correlation between histopathological and radiological response. The radiological response of the primary tumor as defined by RECIST v1.1 criteria (taken for target lesion, only the primary tumor) will be compared with the histopathological response as defined by TRG-Ryan. Evaluation of this correlation will be centralized and carried out by the Central Review Committee of Radiology and Pathology; (viii) The 5-point regression grading system [22] adapted to CC by our team in a pilot study [15], will also be evaluated in this trial. This assessment will be centralized and carried out independently and blindly (without knowing the treatment arms) by 2 of the 3 members of our Central Review Committee of Pathology. This assessment will determine the inter-observer reproducibility of this grading system in CC after chemotherapy and to assess the specificity of histological "regression" criteria using this grading system. Comparison of the reproducibility (test of concordance) of the two systems of grading regression (TRG-Ryan and TRG-Mandard) will identify the most appropriate system for assessing response to chemotherapy in CC.

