The aim of our phase II ECKINOXE study is to evaluate the efficacy (response rate) and tolerability of two regimens of neoadjuvant chemotherapy among patients with locally advanced CC. The control arm will consist of patients treated with FOLFOX-4 post-operatively. This study will allow us to investigate the feasibility and effectiveness of this original neo-adjuvant strategy, and to select the best regimen to improve long-term disease-free and overall survivals. A similar study testing another anti-EGFR monoclonal antibody (Panitumumab) is currently ongoing in the United Kingdom (FOxTROT trial). The pilot stage of this randomised controlled trial on the first 150 included has been recently published. Nearly 90 % (85 of 95) of patients in this trial completed preoperative chemotherapy with grade 3–4 gastrointestinal toxicity in 7 %. All 99 tumours in the preoperative group were resected, with no significant differences in postoperative morbidity between the preoperative and control groups. T3 or more advanced tumours was pathologically confirmed in 98 % of patients undergoing immediate surgery and 91 % of patients following preoperative chemotherapy (p = 0 · 10). Preoperative therapy resulted in significant downstaging in terms of TNM stage compared with the postoperative group (p = 0 · 04), including two pathological complete responses.

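### Time to QoL deterioration censors death, and the follow-up wording lets centres stop at relapse, so censoring on this secondary endpoint can depend on outcome

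*Protocol article*

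**What the plan says.** Two sections of the protocol article bear on this point.

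**Endpoints (secondary endpoints, quality of life).** Questionnaires are given at inclusion, after neoadjuvant chemotherapy, "at 1 month after surgery and every 6 months thereafter". No stop at recurrence is stated. Time to QoL deterioration is the "time interval between randomization and first decrease in QoL score greater or equal to 5 points". The censoring rule is: "Patients without QoL decrease greater or equal to 5 points will be censored at the last follow-up". Neither relapse nor death is an event, and the rule makes no exception for them. In the same list, recurrence-free survival runs to the "date of first recurrence (local, regional or metastatic) or date of death (all causes) if no recurrence", and disease-free survival also counts death without recurrence.

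**Data collection and follow-up.** For all patients, "follow-up assessment will be performed until recurrence and/or death". The six-monthly items are "tumor assessment, CEA measurement, survival status, additional cancer therapy". After the 3-year assessment, "the follow-up will be systematic and performed thereafter this period according to the good clinical practices".

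**The concern.** Ordinary censoring assumes that a censored patient has the same later risk of deterioration as those still observed. Death breaks that assumption in principle, and relapse is likely to break it in practice because it tends to worsen QoL. If patients leave observation at relapse or death with no fall recorded, the analysis treats them as represented by the patients who remain well.

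At stake is the randomised comparison of QoL between immediate surgery and the neoadjuvant arms. If relapse or death comes earlier or more often in one arm, that arm loses more poor-prognosis patients to censoring and can look better on time to deterioration. If centres read the stopping rule differently, the amount of post-relapse QoL data will also vary by centre. Questionnaires not given after relapse cannot be recovered later.

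**Working it through.** The plan gives no figure for this endpoint, so there is none to reproduce. The check sets the rules side by side and then gauges the possible scale.

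**Step 1. What happens to a patient with no recorded 5-point fall**

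| Patient's course | Follow-up stops at relapse | Follow-up continues to death |
|---|---|---|
| Relapses, alive | Censored at relapse; later falls unseen | Still observed; later falls can be recorded |
| Relapses, then dies | Censored at relapse | Censored at last follow-up if still no fall |
| Dies without relapse | Censored | Censored |
| Alive, no relapse | Censored at last follow-up | Censored at last follow-up |

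The third row is the same under both readings, so the treatment of death does not depend on how the follow-up sentence is understood. The first two rows do depend on it.

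**Step 2. Is the follow-up sentence settled elsewhere?** It is not. If follow-up always ran to death, naming recurrence would add nothing. If it always stopped at recurrence, the item on further cancer therapy would lose much of its purpose, and the open-ended QoL schedule would be cut short without saying so. A centre that stops and a centre that continues both comply with the text.

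**Step 3. Ceiling on relapses per group.** Inputs: 33 patients per arm within each RAS group (Statistical analysis and sample size) and a 20 to 30 % recurrence risk (Abstract and Background), treated here as a 3-year risk, which is an assumption.

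- 0.20 × 33 = 6.6
- 0.30 × 33 = 9.9

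Only those with no earlier recorded fall matter for QoL, and the article does not give that share. A simulation assumed independent exponential times, 6-monthly visits, a 36-month horizon and a 3-year probability of deterioration between 30 % and 70 %. With a stop at relapse, it left between 4.3 of 33 patients (70 % deterioration, 20 % relapse) and 8.6 of 33 (30 % deterioration, 30 % relapse) censored at relapse without an observed fall. It did not model the early questionnaires after chemotherapy and surgery. If many falls occur at that point, the number is lower.

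**Step 4. How much the handling can matter.** Let p be the 3-year probability of a fall apart from relapse, and q the probability of relapse or death. If the two are independent:

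- with relapse or death censored, Kaplan-Meier estimates p;
- with relapse or death counted as an event, the figure is 1 − (1 − p)(1 − q);
- the gap is q(1 − p).

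| p | q | Censored | Counted as event | Gap |
|---|---|---|---|---|
| 0.50 | 0.20 | 50 % | 60 % | 10 points |
| 0.50 | 0.30 | 50 % | 65 % | 15 points |
| 0.70 | 0.20 | 70 % | 76 % | 6 points |
| 0.30 | 0.30 | 30 % | 51 % | 21 points |

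The simulation agrees with these values. The gap is a difference between two quantities and is not in itself a bias.

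**Step 5. Direction between arms.** Take p = 0.50 in two arms, with q = 0.20 in one and 0.30 in the other. As an extreme assumption, suppose every relapse is promptly followed by a 5-point fall. Continued questionnaires would then show about 60 % and 65 % deteriorated. Stopping at relapse and censoring would show 50 % in both, so the 5-point disadvantage disappears. The documents do not say how often relapse brings such a fall. The example shows only the direction.

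**The case against.** The strongest reply is that the text may already intend what is asked for. The follow-up sentence can mean continuing to death, vital status and further therapy are recorded every 6 months, follow-up goes on after 3 years, and the QoL schedule has no stop at relapse. This stands to the extent that a reader might infer that follow-up ends at recurrence and that survival after relapse is not collected, and the article supports neither as a settled rule. The accurate statement is that collection after relapse is not assured.

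A reader might go further and say that overall survival is compromised. It is not a listed endpoint. It appears only in the Discussion, where the aim is "to select the best regimen to improve long-term disease-free and overall survivals", and the article names no endpoint for the possible phase III.

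A reader might also apply the article's prognostic figures to all 165 patients: 0.20 × 165 = 33, or, with the 43 % disease-free survival from the cited CT poor-prognosis group, 0.57 × 165 = 94. That counts everyone who relapses or dies, including patients whose fall was recorded earlier, and the upper figure comes from another series. It is not the number affected on QoL.

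Two further replies carry weight. An endpoint of deterioration alone and a composite with death answer different questions, so the choice between them is partly one of estimand. Competing-risk handling and sensitivity analyses are also commonly left to an analysis plan. Neither reply removes the point. The article itself fixes the censoring rule and the wording on the end of follow-up, and no analysis plan can supply questionnaires that were never given.

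**Conclusion.** The point holds in limited form. It is certain from the text that a death without a recorded 5-point fall is treated as non-informative censoring, whereas both survival endpoints in the same list count death without recurrence as an event. It is also certain that the follow-up wording permits stopping at relapse and conflicts with the open-ended QoL schedule and the six-monthly items. Where centres do stop, QoL censoring depends on an event likely to worsen QoL, and the arm with more early relapses or deaths can look better.

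The size is unknown. At 20 to 30 % recurrence, at most about 7 to 10 of 33 patients per group relapse, and fewer are censored at relapse without an earlier fall. The effect may be small on scales that drop early. The 6 to 21 point gaps in the working rest on assumed deterioration rates and independence, and they show sensitivity to the definition, not demonstrated bias. The primary tumour-regression endpoint is untouched. Recurrence-free and disease-free survival are also unaffected, since both are complete at the first event.

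**What to change.** **Data collection and follow-up.** State that QoL questionnaires, vital status and further cancer therapy continue to be collected after recurrence, for all randomised patients, to at least 3 years or death.

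**Endpoints, quality of life.** Analyse time to QoL deterioration in two versions: a composite in which death without prior deterioration is an event, and one in which such deaths are censored. Say which is the main analysis and which is the sensitivity analysis.

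The cost is a few sentences of text, plus continued 6-monthly questionnaires and vital-status checks for patients who have relapsed. No change to sample size or to the primary analysis is needed.

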### Statistical analysis and sample size

Patients RAS Wild Type will be randomized between arm A, B and C whereas RAS mutated patients will be only randomized between arm A and arm C. According to Simon (Optimax) 2 steps design, it will be required to include 33 patients/ arm (with unilateral alpha type one error of 5 % and a power of 95 %) to test following hypotheses: (i) H_0_: an histological response (TRG1-Ryan) rate of 10 % is uninteresting; (ii) H_1_: an histological response (TRG1-Ryan) higher than 10 % is required to rate pursue investigations in phase III trial. A response rate of 35 % is expected.

At the first step (interim analysis), after inclusion of the first 13 patients in each arm, if the number of histological response (TRG1-Ryan) is ≤ 1, inclusion in this arm will be stopped and if the number of histological response (TRG1-Ryan) is ≥ 2, inclusion of the next 20 patients will be done. Calculated power at the interim analysis is 97 %.

At the 2^nd^ step (final analysis), after inclusion of 33 patients in each arm, if the number of histological response (TRG1-Ryan) is ≤ 6, this arm will be declared uninteresting for further investigations in phase III trial and if the number of histological response (TRG1-Ryan) is ≥ 7, this arm will be declared interesting for further investigations in phase III trial. At the second step calculated power will be 96.3 % and alpha type one error will be 2 %. In control arm no interim analysis is plan for efficacy. Then in this arm, at the second step, calculated power will be 97.2 % and alpha type one error will be 4.2 %. If ≥ 10 % of complications ≥ grade III (Clavien and Dindo classification) within 60 postoperative days are reported, this arm will be declared unsafe.

Interim and final results of this phase II study will be reviewed by an independent data monitoring committee (IDMC). Trial will be pursued in phase III with 2 or 3 arms according to IDMC recommendations. Control arm (no neoadjuvant treatment) will be kept as control arm in phase III whatever the results of phase II study. Required number of patients is 33 × 3 = 99 patients for RAS WT patients and 33 × 2 = 66 for those with RAS mutated. Taking into account prevalence of RAS WT patients of 50 %, it will be necessary to screen 192 patients to obtain 99 patients RAS WT and 66 patients mutated for RAS with a minimal probability of 90 %.

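### The second-step power (96.3 %) and type I error (2 %) given for the neoadjuvant arms are wrong: the 1/13, 6/33 rule has power 95.0 % and type I error 3.7 %

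*Protocol article*

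**What the plan says.** All the relevant statements are in the protocol article, section on statistical analysis and sample size.

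- **Hypotheses.** The null is that "an histological response (TRG1-Ryan) rate of 10 % is uninteresting". For the alternative, "A response rate of 35 % is expected".
- **Targets.** Under a two-step Simon design, "it will be required to include 33 patients/ arm (with unilateral alpha type one error of 5 % and a power of 95" %.
- **Stage 1.** The stopping condition is "after inclusion of the first 13 patients in each arm, if the number of histological response (TRG1-Ryan) is ≤ 1". If instead the count "TRG1-Ryan) is ≥ 2, inclusion of the next 20 patients will be done". The text adds: "Calculated power at the interim analysis is 97" %.
- **Stage 2.** The negative verdict applies "after inclusion of 33 patients in each arm, if the number of histological response (TRG1-Ryan) is ≤ 6, this arm will be declared uninteresting"; 7 or more responses make the arm interesting for phase III.
- **Operating characteristics of the two-stage rule.** "At the second step calculated power will be 96.3 % and alpha type one error will be 2" %.
- **Control arm.** There is no interim look for efficacy, and the section gives 97.2 % power and 4.2 % type I error.

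**The concern.** The neoadjuvant arms and the control arm share the same final cut-off, 7 or more of 33. The only difference is the stop at 13 patients. A futility stop lowers both the type I error and the power, because it removes trial paths that would otherwise have reached 7 responses. According to the article, this stop cuts the type I error by more than half (4.2 % to 2 %) and costs only 0.9 points of power (97.2 % to 96.3 %). A stop at 1 or fewer of 13 cannot plausibly do that.

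These are the stated error rates of the primary go/no-go decision on TRG1. The independent data monitoring committee is to rule on efficacy using the Simon criteria and to recommend a phase III with two or three arms. A committee member reading this section would take the chance of carrying an inactive regimen forward as 2 % per arm, and the chance of missing a 35 % response rate as 3.7 %.

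**Working it through.** **Inputs**, all from the section on statistical analysis and sample size: p0 = 0.10; p1 = 0.35; n1 = 13, stop at ≤ 1; 20 further patients, so n = 33; interesting at ≥ 7.

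**Step 1. Reproduce the plan's neighbouring figures.**

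- Interim: P(X ≥ 2 | n = 13, p = 0.35) = 0.9704. Stated 97 %.
- Control arm, single stage: P(X ≥ 7 | n = 33, p = 0.35) = 0.9717. Stated 97.2 %.
- Control arm, single stage: P(X ≥ 7 | n = 33, p = 0.10) = 0.0417. Stated 4.2 %.

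All three match to the printed precision, so the hypotheses, cut-offs and method are read as the authors meant them.

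**Step 2. The two-stage rule.** The probability of declaring an arm interesting is

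Σ (x = 2 to 13) P(X1 = x | 13, p) × P(X2 ≥ 7 − x | 20, p).

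| Stage 1 responses x | p = 0.10: P(X1 = x) × P(X2 ≥ 7 − x) | p = 0.35: P(X1 = x) × P(X2 ≥ 7 − x) |
|---|---|---|
| 2 | 0.24477 × 0.04317 = 0.01057 | 0.08361 × 0.88180 = 0.07373 |
| 3 | 0.09972 × 0.13295 = 0.01326 | 0.16508 × 0.95562 = 0.15776 |
| 4 | 0.02770 × 0.32307 = 0.00895 | 0.22223 × 0.98788 = 0.21953 |
| 5 | 0.00554 × 0.60825 = 0.00337 | 0.21539 × 0.99787 = 0.21493 |
| 6 | 0.00082 × 0.87842 = 0.00072 | 0.15464 × 0.99982 = 0.15461 |
| 7 or more | 0.00010 | 0.12948 |
| **Total** | **0.0370** | **0.9500** |

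The type I error is 3.70 % (stated 2 %) and the power is 95.00 % (stated 96.3 %).

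**Step 3. Cross-check against the control arm.** The stop can remove only those paths with 0 or 1 response in 13 that would still have reached 7 in 33.

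- At p = 0.10: 0.25419 × 0.00239 + 0.36716 × 0.01125 = 0.0047, and 0.0417 − 0.0047 = 0.0370.
- At p = 0.35: 0.00370 × 0.58337 + 0.02588 × 0.75460 = 0.0217, and 0.9717 − 0.0217 = 0.9500.

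So the stop lowers the type I error by about 0.5 points and the power by about 2.2 points. The printed figures imply falls of 2.2 and 0.9 points.

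**Step 4. Could another reading give the printed pair?**

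| Reading | Power | Type I error |
|---|---|---|
| Stated | 96.3 % | 2 % |
| Conditional on passing stage 1 | 97.9 % | 9.8 % |
| Final cut-off ≥ 8 | 91.8 % | 1.3 % |
| Final cut-off ≥ 6 | 96.4 % | 8.7 % |

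None does. A search over every single futility look, at any stage-1 size from 1 to 32 and any stopping bound, with the 7-of-33 rule kept, gives the same answer. Among looks with a type I error below 2.5 %, the highest power is 92.6 %. Among looks with power of at least 96.25 %, the lowest type I error is 3.6 %.

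**Step 5. Probable origin.**

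- 1 − 0.0370 = 0.9630, the number printed as power.
- P(pass stage 1, then ≤ 6 of 33 | p = 0.35) = 0.9704 − 0.9500 = 0.0204, the number printed as type I error.

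It therefore appears that the complement of the type I error was labelled power, and the second-stage part of the type II error was labelled alpha. This is inferred from the arithmetic; the article does not say so.

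**The case against.** The strongest reply is that nothing operational changes. The governing targets are a one-sided 5 % and 95 % power, and the true 3.7 % and 95.00 % meet both. A search over Simon designs for these inputs returns 1/13, 6/33 as the design with the smallest expected sample size under the null (20.6 patients), so the design itself was correctly derived. No patient is treated differently and no arm receives a different verdict. A reader who relies on the 5 % ceiling is not misled about the maximum false-go risk. The power gap is only 1.3 points, and the move to phase III also depends on the committee's recommendation and on a separate safety criterion.

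All of that stands, and it limits the consequence. It is also fair that the printed numbers are quantities of this design under wrong labels, and that the exchange of labels is inferred. None of it makes the sentence correct. It gives specific calculated values for the primary decision rule, both are wrong, and both err in the favourable direction.

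**Conclusion.** The concern holds. Over both stages the rule has a type I error of 3.7 %, not 2 %, and a power of 95.0 %, not 96.3 %. The type I error is the material part: it is understated by 1.7 points, and the true value is 1.85 times the stated one (3.70 / 2). The type II error is 5.0 % where the text implies 100 − 96.3 = 3.7 %.

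This rests on the article's own 10 % and 35 % response rates, its cut-offs, independent binomial responses, and adherence to the stage-1 stop. The defect is a false statement of operating characteristics, not a faulty design: the targets are met, although power reaches 95 % with almost nothing to spare (0.95003).

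**What to change.** Replace the sentence with wording such as: *Over both stages the design has 95.0 % power at a response rate of 35 % and a type I error of 3.7 % at 10 %; the probability of stopping at the first stage is 62 % under H0 and 3 % under H1.* The stopping probabilities are 1 − 0.3787 = 0.621 and 1 − 0.9704 = 0.030.

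The cut-offs, the 33 patients per arm, the interim figure and the control-arm figures stay as they are. The cost is one sentence and slightly less favourable stated error rates. If the same pair of figures appears in the full protocol, the analysis plan or the monitoring committee's documents, correct it there too.

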**Methods/Design:**

PRODIGE 22 - ECKINOXE is a multicenter randomized phase II trial designed to evaluate efficacy and feasibility of two chemotherapy regimens (FOLFOX-4 alone and FOLFOX-4 + Cetuximab) in a peri-operative strategy in patients with bulky CCs. Patients with CC deemed as high risk T3, T4 and/or N2 on initial abdominopelvic CT scan are randomized to either colectomy and adjuvant chemotherapy (control arm), or 4 cycles of neoadjuvant chemotherapy with FOLFOX-4 (for *RAS* mutated patients). In *RAS* wild-type patients a third arm testing FOLFOX+ cetuximab has been added prior to colectomy. Patients in the neoadjuvant chemotherapy arms will receive postoperative treatment for 4 months (8 cycles) to complete their therapeutic schedule. The primary endpoint of the study is the histological Tumor Regression Grade (TRG) as defined by Ryan. The secondary endpoints are: treatment strategy safety (toxicity, primary tumor related complications under chemotherapy, peri-operative morbidity), disease-free and recurrence free survivals at 3 years, quality of life, carcinologic quality and completeness of the surgery, initial radiological staging and radiological response to neoadjuvant chemotherapy, and the correlation between histopathological and radiological response. Taking into account a 50 % prevalence of CC without *RAS* mutation, accrual of 165 patients is needed for this Phase II trial.

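### At the stated 50 % RAS wild-type prevalence, screening 192 patients yields 99 wild-type and 66 mutated patients with probability about 36 %, not at least 90 %

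*Protocol article*

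**What the plan says.** All the figures stand together in the protocol article under Statistical analysis and sample size.

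- **Per-arm size:** "it will be required to include 33 patients/ arm".
- **Wild-type target:** "Required number of patients is 33 × 3 = 99 patients for RAS WT patients".
- **Mutated target:** "33 × 2 = 66 for those with RAS mutated".
- **Prevalence:** "Taking into account prevalence of RAS WT patients of 50" %.
- **Screening number:** "it will be necessary to screen 192 patients to obtain 99 patients RAS WT and 66 patients mutated for RAS".
- **Assurance attached to that number:** "with a minimal probability of 90" %.

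The abstract (Methods/Design) gives the same prevalence and the sum of the two targets: "Taking into account a 50 % prevalence of CC without *RAS* mutation, accrual of 165 patients is needed for this Phase II trial". That total, 99 + 66 = 165, is correct.

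**The concern.** The claim fails on inspection. With half of patients wild-type, 192 screened patients give 96 wild-type patients on average, and 99 are needed. A target above the mean of a symmetric distribution is reached less than half the time, so 90 % is out of reach. The 50 %, the 192 and the 90 % cannot all be right.

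What is at stake is the planning of screening and accrual. The wild-type stratum feeds three arms. Under Randomisation, Arm B takes only wild-type patients, so a surplus of mutated patients cannot make good a shortfall there.

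**Working it through.** **Inputs, all from Statistical analysis and sample size:** wild-type target 99; mutated target 66; wild-type prevalence p = 0.5; number screened n = 192; stated probability at least 0.90.

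**Model.** Let X be the number of wild-type patients among n screened, with X ~ Binomial(n, p). Everyone else is mutated, so both targets are met when 99 ≤ X ≤ n − 66. This counts every screened patient as eligible, consenting and with a RAS result, which favours the plan.

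**Attempt to reproduce the stated figure (n = 192, p = 0.5).**

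- Mean of X = 192 × 0.5 = 96. Variance = 192 × 0.25 = 48, so SD = 6.93.
- P(X ≥ 99) = 0.3592.
- P(mutated ≥ 66) > 0.9999.
- Joint: P(99 ≤ X ≤ 126) = 0.359.
- Normal approximation: 1 − Φ((98.5 − 96)/6.93) = 0.359 with continuity correction; 1 − Φ((99 − 96)/6.93) = 0.333 without.
- Exchanging the two targets gives the same 0.359 by symmetry.

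Only the mutated target taken alone passes 90 %. The sentence requires both targets, and the wild-type one is binding.

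**Number that does give 90 % at p = 0.5.**

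| n screened | P(both targets met) |
|---|---|
| 192 | 0.359 |
| 198 | 0.528 |
| 205 | 0.712 |
| 210 | 0.815 |
| 215 | 0.890 |
| 216 | 0.902 |

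The smallest n is 216. The gap is 216 − 192 = 24, and 24/192 = 12.5 %. Even n = 198, where the expected wild-type count equals the target (198 × 0.5 = 99), gives only 53 %.

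**Sensitivity to prevalence.**

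| Wild-type prevalence | P(both met), n = 192 | Smallest n for 90 % |
|---|---|---|
| 45 % | 0.040 | 241 |
| 50 % | 0.359 | 216 |
| 55 % | 0.847 | 196 |
| 56 % | 0.902 | 192 |
| 58 % | 0.957 | 187 |
| 60 % | 0.946 | 188 |
| 61 % | 0.915 | 191 |
| 61.5 % | 0.893 | 193 |

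The required n falls to 187 and then rises as the mutated target becomes binding. It therefore equals 192 at about 56 % and again just above 61 %.

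**If screening did stop at 192.** The wild-type cohort would be short with probability 1 − 0.359 = 0.641. The expected shortfall is about 4.5 patients over three arms, or 4.5/3 = 1.5 per arm. The table below keeps the plan's rules (stop at 1 or fewer responses in 13; success at 7 or more at the end), with response rates of 10 % under H0 and 35 % expected:

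| Patients in a two-stage arm | Power at 35 % | Type I error at 10 % |
|---|---|---|
| 33 | 95.0 % | 3.7 % |
| 32 | 94.4 % | 3.2 % |
| 31 | 93.5 % | 2.8 % |
| 30 | 92.5 % | 2.4 % |

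**The case against.** The strongest reply is that 192 is a forecast, not a design parameter. The design is fixed at 33 included patients per arm, the final decision is taken once they are in, and nothing in the article says that screening ends at 192. If screening goes on until the arms are full, the trial's operating characteristics are intact. This stands, and it limits the consequence.

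A reader might infer that the cut-off of 7 responses in 33 loses its stated error rates. The document does not support that. It would need a hard stop at 192, which is not stated. Even then, at 30 per arm, power is 92.5 % and the type I error falls, so false positives do not increase.

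A reader might also infer that the authors really assumed 56 %. That prevalence does fit, but so does one just above 61 %, and the article gives 50 % in both places. Where 192 came from cannot be settled from the text.

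It can also be said that 99 is a maximum, because an experimental arm with 1 or fewer responses among its first 13 patients stops including; at a 10 % response rate this happens with probability 0.62. So 192 may be enough for the patients actually needed more often than 36 % of the time. That is fair, but the sentence promises the full 99 and 66, and for those the probability is as computed.

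**Conclusion.** The stated figure is wrong. With 50 % wild-type prevalence and 192 screened, the probability of obtaining 99 wild-type and 66 mutated patients is about 36 %, against a stated minimum of 90 %. Reaching 90 % takes 216. Nothing elsewhere in the article corrects this.

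The result rests on the article's own inputs and on independent patients who are all eligible and have a RAS result. Any screen failure lowers the probability and raises the number needed.

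This is an error in a planning figure, not a flaw in the test. The 33 per arm, the total of 165 and the decision rules stand. Accrual planned around 192 will probably run over, since filling the wild-type stratum alone takes 99/0.5 = 198 screened patients on average. A shortfall in the wild-type arms, with a modest loss of power, follows only if screening is closed at 192.

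**What to change.** In Statistical analysis and sample size, make the three figures agree in one of these ways:

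1. Keep 50 % and 90 %, and restate the screening number as 216 (probability 90.2 %), saying that this allows for no screen failures.
2. Keep 50 % and 192, and state the probability as about 36 %.
3. If a prevalence other than 50 % was assumed, state it, justify it from data rather than from its fit to 192, and change it in the abstract as well.

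It would help to add that screening continues until each RAS stratum is filled, if that is the intention.

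The cost is one corrected sentence and, under option 1, 24 more patients to plan for at screening. The number of randomised patients does not change.
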